**Table 4. Toxicokinetic parameters in 4-week repeated dose intravenous toxicity study in cynomolgus monkeys**

| Dose (mg/kg) | Time  | Gender | C max (mg/mL) | AUC 0-168h (hmg/mL) |
|--------------|-------|--------|--------------------------|--------------------------------|
| 20           | First | Female | 0.467 ± 0.0911           | 15.9 ± 3.97                    |
|              |       | Male   | 0.484 ± 0.116            | 17.4 ± 5.40                    |
|              | Last  | Female | 0.282 ± 0.222            | 4.74 ± 6.53                    |
|              |       | Male   | 0.366 ± 0.284            | 15.3 ± 17.4                    |
| 60           | First | Female | 1.36 ± 0.126             | 43.9 ± 8.56                    |

|     |       |        |                  |                 |
|-----|-------|--------|------------------|-----------------|
| 200 | Last  | Male   | $1.43 \pm 0.212$ | $52.8 \pm 13.0$ |
|     |       | Female | $1.48 \pm 0.398$ | $45.8 \pm 17.0$ |
|     |       | Male   | $1.25 \pm 0.459$ | $35.9 \pm 19.7$ |
|     | First | Female | $5.96 \pm 0.640$ | $176 \pm 31.2$  |
|     |       | Male   | $4.42 \pm 0.772$ | $168 \pm 35.4$  |
|     | Last  | Female | $5.50 \pm 1.32$  | $209 \pm 86.7$  |
|     |       | Male   | $5.62 \pm 1.11$  | $210 \pm 40.8$  |

[figure not shown]

**Figure 2 Mean concentration-time curve of TQB2858 in serum of cynomolgus monkeys after intravenous injection of TQB2858**

After the first administration, the mean serum  $AUC_{0-168h}$  of female monkeys in each group was 15.9, 43.9 and 176 h mg/mL, respectively, with a ratio of 1:2.8:11.1;

the mean serum AUC0-168h of male monkeys was 17.4, 52.8 and 168 h mg/mL, respectively, with a ratio of 1:3.0:9.7. The mean AUC0-168h ratios of this product in the serum of female and male monkeys in each group were 0.9, 0.8, and 1.0. The mean AUC0-168h of TQB2858 in the serum of female monkeys in each group was 4.74, 45.8 and 209 hmg/mL, respectively, with a ratio of 1:9.7:44.1; the mean AUC0-168h of TQB2858 in the serum of male monkeys was 15.3, 35.9 and 210 hmg/mL, respectively, with a ratio of 1:2.3:13.7. The mean AUC0-168h ratios of this product in the serum of female and male monkeys in each group were 0.3, 1.3, and 1.0. Compared with the first dose, the mean AUC0-168h ratios of this product in the serum of female monkeys in each group were 2.6, 2.1, and 2.0, respectively, and those of male monkeys were 2.7, 2.2, and 2.1, respectively. Compared with the first dose, the mean individual AUC0-168h ratios of TQB2858 in serum were 0.3, 1.0 and 1.2 in female monkeys and 1.2, 0.7 and 1.3 in male monkeys in each group, respectively.

In the dose range of 20 ~ 200 mg/kg, this product was immunogenic to cynomolgus monkeys; except that the mean AUC0-168h in female monkeys in the 20 mg/kg group was lower than that in male monkeys, there was no significant gender difference at the other doses after the first and last doses; except that the mean AUC0-168h in female monkeys in the 20 ~ 60 mg/kg dose range increased slightly more than dose proportionally, the mean AUC0-168h in monkeys in the first and last doses increased basically in accordance with dose proportionally. No significant accumulation was seen. After intravenous infusion in cynomolgus monkeys, anti-drug antibodies were detected after drug administration in 9 (9/10), 9 (9/10) and 3 (3/10) animals in each dose group, respectively. The production of anti-drug antibodies affected the evaluation of sex difference and accumulation index.

#### **1.4 Advance in Clinical Research**

The phase I study TQB2858-I-01 (CDE clinical trial registration number CTR20210612) of TQB2858 injection was conducted in Jilin Cancer Hospital. The study was formally initiated on April 12, 2021, and the first subject was completed on April 20, 2021. By July 1, 2021, a total of 6 subjects have been enrolled, including 1 subject in the 3 mg/human dose group, 1 subject in the 60 mg/human dose group, and

4 subjects in the 600 mg/human dose group (1 subject dropped out due to personal reasons, and 1 subject was added). At present, there are two CTCAE grade 1 rashes in the 600 mg/person dose group, which can subside spontaneously without the need for drug intervention. The rest had no adverse events. It suggests good safety. The 1200 mg/person dose group has now been initiated.

## **2. Trial objectives and endpoints**

### **2.1 Primary objective**

- To evaluate the preliminary efficacy of TQB2858 injection in subjects with advanced high-grade sarcoma.

### **2.2 Secondary objectives**

- Evaluation the safety of TQB2858 injection in subjects with advanced high-grade sarcoma;

### **2.3 Exploratory objectives**

- To explore biomarkers associated with treatment of TQB2858 injection.

### **2.4 Primary Endpoints**

- ORR based on RECIST 1.1 and iRECIST;

### **2.5 Secondary Endpoints**

- Other efficacy indicators (based on RECIST 1.1 and iRECIST): 3-month ORR, PFS, DCR, DOR, OS;
- Incidence of adverse events: occurrence of all adverse events (AEs), serious adverse events (SAEs) and treatment-related adverse events (TEAEs);

### **2.6 Exploratory Endpoints**

To detect the biomarkers related to TQB2858 injection treatment, such as the expression of CD68, C D163 , C D206 , I RF8 , C D3 , C D8 , P D-L1 , C D20 , C D56 , B 7-H3 , C D47 , C D4 etc. in tumor tissues, and the proportion of tertiary lymph nodes was evaluated.

## **3. Study Design**

This Phase Ib clinical trial was conducted based on the RP2D determined in the

Phase I dose escalation and cohort expansion clinical study of TQB2858 injection. It is planned to enroll 30-100 patients with advanced high-grade sarcoma (Cohort 1:10-30 patients with primary alveolar soft part sarcoma; Cohort 2:10-30 patients with alveolar soft part sarcoma failing PD-1 therapy; Cohort 3:10-40 patients with other subtypes (pleomorphic sarcoma, classical osteosarcoma, Yuventus sarcoma, chondrosarcoma, dedifferentiated liposarcoma, etc.)). To assess the preliminary efficacy and safety of TQB2858 injection in subjects with advanced high-grade sarcoma.

## **4. Subject Selection and Withdrawal**

### **4.1 Inclusion criteria of subjects**

Patients who meet all of the following inclusion criteria can be included in this trial:

- 1) Histologically confirmed unresectable, recurrent, or metastatic high-grade sarcoma;
- 2) Patients who previously received at least one line of treatment, with disease progression or intolerance during treatment, or disease progression after the end of treatment; (except for alveolar soft part sarcoma and clear cell sarcoma)
  - a) Cohort 1: Primary alveolar soft part sarcoma;
  - b) Cohort 2: alveolar soft part sarcoma failing PD-1 therapy;
  - c) Cohort 3: Other subtypes (pleomorphic sarcoma, classic osteosarcoma, Ewing sarcoma, chondrosarcoma, dedifferentiated liposarcoma, etc.)
- 3) Age: 18-70 years old;
- 4) ECOG score: 0 ~ 1;
- 5) Life expectancy of more than 3 months;
- 6) Normal function of major organs meeting the following criteria:
  - a) Hematology (not transfused and not receiving growth factor support before screening): hemoglobin (HGB)  $\geq 80$  g/L; neutrophil count (NEUT)  $\geq 1.5 \times 10^9$ /L; platelet count (PLT)  $\geq 90 \times 10^9$ /L;
  - b) Biochemistry: alanine aminotransferase (ALT) and aspartate aminotransferase (AST)  $\leq 2.5 \times$  ULN (ALT and AST  $\leq 5 \times$  ULN for patients with primary hepatobiliary tumors or liver metastases); total bilirubin (TBIL)  $\leq 1.5 \times$  ULN

- (TBIL  $\leq 3 \times$  ULN for patients with Gilbert's syndrome); creatinine (CRE)  $\leq 1.5 \times$  ULN or creatinine clearance  $\geq 60$  ml/min;
- c) Coagulation function: activated partial thromboplastin time (APTT), international normalized ratio (INR), prothrombin time (PT)  $\leq 1.5 \times$  ULN;
- d) Left ventricular ejection fraction (LVEF)  $\geq 50\%$ ;
- 7) Female patients of childbearing potential must have a negative serum or urine HCG test within 7 days prior to enrollment and must be non-lactating; patients should agree to take contraceptive measures during the study and within 6 months after the end of the study period;
- 8) The patient voluntarily joined the study, signed the informed consent form, and had good compliance.

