  - 5. Patients with renal failure requiring hemodialysis or peritoneal dialysis;
  - 6. History of immunodeficiency, including HIV positive or suffering from other acquired, congenital immunodeficiency diseases, or history of organ transplantation;
  - 7. Poorly controlled diabetes (fasting blood glucose (FBG)  $> 10$  mmol/L);
  - 8. Urinalysis showed urine protein  $\geq ++$ , and confirmed 24-hour urine protein  $> 1.0$  g;
  - 9. Patients with epilepsy requiring treatment;
- 2) Tumor related symptoms and treatment:
  - a) Patients who previously received surgery, chemotherapy, radiotherapy or other anti-cancer therapy 4 weeks before the start of study treatment (the washout

period will be calculated from the end time of treatment); patients who previously received local radiotherapy can be eligible if: the end of radiotherapy is more than 4 weeks from the start of study treatment (more than 2 weeks for brain radiotherapy); and the target lesion selected for this study is not in the radiotherapy area; or the target lesion is located in the radiotherapy area, but progression has been confirmed.

- b) Patients who have received Chinese patent medicines with anti-tumor indications (including compound cantharidin capsules, Kangai injection, Kanglaite capsules/injection, Aidi injection, Brucea javanica oil injection/capsules, Xiaoer Fangye/injection, cinobufotalin capsules, etc.) in the package insert of NMPA approved drugs 2 weeks before the start of study treatment;
  - c) Uncontrolled pleural effusion, pericardial effusion or ascites requiring repeated drainage (judged by the investigator);
  - d) Patients with brain metastasis whose symptom control is stable for less than 4 weeks after stopping dehydrating agents and steroid drugs;
- 3) Study Treatment Related:
- a) History of live attenuated vaccination 28 days before the start of study treatment or planned live attenuated vaccination during the study;
  - b) Previous history of severe allergy to macromolecular drugs, or allergy to known components of TQB2858 injection;
  - c) Active autoimmune disease requiring systemic therapy (eg, use of disease-modifying drugs, corticosteroids, or immunosuppressive agents) within 2 years of the start of study treatment. Replacement therapy (e.g., thyroxine, insulin, or physiological corticosteroids for adrenal or pituitary insufficiency, etc.) is not considered systemic;

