In this study, we preliminarily investigated the therapeutic effect of TQB2858 injection in advanced high-grade sarcoma and assessed the efficacy according to RECIST 1.1 evaluation criteria and iRECIST evaluation criteria. Indicators include objective response rate (ORR), disease control rate (DCR), progression-free survival (PFS), 3-month ORR, overall survival (OS) and duration of response (DOR).

- 1) Objective response rate (ORR): is the proportion of subjects whose tumor volume reduction reaches the prespecified value and maintains the minimum time limit (at the next imaging assessment), including cases of complete response (CR) and partial response (PR);
- 2) Disease control rate (DCR): the proportion of patients whose tumors shrink or remain stable for a certain period of time, including patients with CR, PR and stable disease (SD);
- 3) Progression-free survival (PFS): The time from the first dose to disease progression (PD) or death before PD; if there is no PD or death before PD, the date of the last imaging assessment will be used as the cut-off date;
- 4) Overall survival (OS): The time from the first treatment of a patient to death from any cause.
- 5) DOR: In subjects with CR or PR, the time from the first tumor assessment of CR or PR to PD or death before PD; if a subject with CR or PR did not experience PD or death before PD, the date of the last radiographic assessment will be used as the cut-off date.

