## **11. Statistical Analysis**

## 11.1 Analysis Populations

Full Analysis Set (FAS): All the subjects who were enrolled and took the study drug at least once were included in the FAS. The following situations may lead to the exclusion of the enrolled subjects from the FAS: they did not meet the main criteria; they did not take the study drug once; they did not have any data after enrollment. Full analysis set is used for analysis of baseline and demographic data;

Safety Analysis Set (SS): all subjects who used the study drug at least once and had safety evaluation data; the safety population will be used for the analysis of safety data.

Effective Analysis Set (EAS): all enrolled subjects who have received at least one dose of the study drug and have at least one efficacy evaluation indicator. The purpose of this data set is to analyze the efficacy indicators of subjects.

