### **11.3.7 Evaluation of Anti-tumor Clinical Efficacy**

The anti-tumor efficacy of TQB2858 injection will be preliminarily evaluated in this trial. Efficacy analyses were based on the Efficacy Assessment Analysis Set (EAS). Efficacy evaluation indicators mainly include: objective response rate (ORR), disease control rate (DCR), progression-free survival (PFS), overall survival (OS) and duration of response (DOR), 3-month ORR, etc.

Objective response rate (ORR): The proportion of objective response cases (PR + CR) in the total number of cases and its 95% CI will be calculated. The 95% CI for ORR was calculated based on the exact binomial method using the F-distribution.

Disease control rate (DCR): The proportion of disease control cases (PR + CR + SD) in total cases and its 95% CI will be calculated. The 95% CI for DCR was calculated based on the exact binomial method of the F-distribution.

Progression-free survival (PFS): PFS and its 95% CI were estimated using the Kaplan-Meier method, and Kaplan-Meier curves were plotted.

Overall survival (OS): OS and its 95% CI will be estimated using the Kaplan-Meier method and the Kaplan-Meier curve will be plotted.

Duration of response (DOR): Kaplan-Meier method was used to estimate DOR and its 95% CI, and Kaplan-Meier curve was plotted. Only analyzed for responders.

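### The primary endpoint is RECIST response rate, but no eligibility criterion requires a measurable lesion, so a subject unable to reach partial response can enrol and count in the ORR denominator

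*Protocol*

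**What the plan says.** - **Endpoint.** Protocol Section 2.4 gives the primary endpoint as "ORR based on RECIST 1.1 and iRECIST". Section 8 adds that ORR "is the proportion of subjects whose tumor volume reduction reaches the prespecified value and maintains the minimum time limit".
- **Eligibility.** The disease criterion in Section 4.1 is "Histologically confirmed unresectable, recurrent, or metastatic high-grade sarcoma". The other seven criteria cover prior treatment and cohort, age, performance status, life expectancy, organ function, pregnancy and contraception, and consent. The synopsis carries the same list. None asks for a measurable lesion, and no exclusion in Section 4.2 removes subjects with only non-measurable disease.
- **Where a target lesion appears.** Exclusion 2a, in its exception for prior local radiotherapy, sets the condition that "the target lesion selected for this study is not in the radiotherapy area", or else that progression in the irradiated lesion is confirmed. The imaging instructions for the end of Cycle 2 (Section 6.2.2) also refer to target and non-target lesions. Both assume that a target lesion exists; neither requires one.
- **Analysis.** Section 11.1 defines the efficacy set (EAS) as "all enrolled subjects who have received at least one dose of the study drug and have at least one efficacy evaluation indicator". Section 11.3.7 bases efficacy on this set and states: "The proportion of objective response cases (PR + CR) in the total number of cases and its 95% CI will be calculated".

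**The concern.** A response defined by shrinkage to a set value needs a lesion whose size can be followed. Under RECIST 1.1, which the protocol adopts but does not reproduce, a subject with non-target disease only is rated CR, non-CR/non-PD or PD. Partial response is not available.

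If such a subject is eligible and is counted, the denominator grows by one while the main route into the numerator is closed. ORR is then lowered by who was admitted rather than by what the drug did. Section 11.3.2 plans no hypothesis test, so the estimated ORR and its interval are the trial's main result. A systematic error in that estimate is worth removing when it costs one sentence.

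Cohort 3 is where this is most plausible, because Section 3 names osteosarcoma, Ewing sarcoma and chondrosarcoma. Section 8 also has bone metastases followed by bone scan and does not require a repeat at every assessment unless symptoms worsen.

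**Working it through.** **1. Does the text let such a subject through?** Take a never-irradiated Cohort 3 subject with non-measurable lesions only.

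| Step | Rule | Result |
|---|---|---|
| Enrolment | Section 4.1, eight criteria | Not stopped |
| Exclusion | Section 4.2; 2a applies only after prior local radiotherapy | Not stopped |
| Baseline | Sections 6.1 and 8 require scans, not a measurable lesion | Not stopped |
| EAS | Section 11.1: one dose, one efficacy indicator | Can enter after one assessment |
| ORR denominator | Section 11.3.7: all cases in the EAS | Can be counted |
| ORR numerator | CR or PR | PR unavailable; CR possible |

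**2. The plan's own figure.** The total of 30–100 is the sum of the cohort ranges: 10 + 10 + 10 = 30 and 30 + 30 + 40 = 100. Section 11.2 uses no response rate, so there is no power calculation to reproduce and the sample size does not depend on this point.

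**3. Effect on ORR.** Let p be the ORR in subjects with measurable disease, f the share without it, and c the CR rate in that share.

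Expected ORR = p(1 − f) + c·f

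The worst case sets c = 0, which gives p(1 − f). The documents do not give f; 5–20% is assumed. The p values of 5% and 18% are the bone and soft tissue cohort results of the pembrolizumab study in Section 1.1 (2/40 and 7/40), and 40% is its undifferentiated pleomorphic sarcoma result (4/10). The 20% is a round illustrative value.

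| p | f = 5% | f = 10% | f = 20% |
|---|---|---|---|
| 5% | 4.75% | 4.5% | 4.0% |
| 18% | 17.1% | 16.2% | 14.4% |
| 20% | 19.0% | 18.0% | 16.0% |
| 40% | 38.0% | 36.0% | 32.0% |

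The loss is a fixed proportion f of p. At 18–20% it is about 1 to 4 percentage points; at 40% it is 2 to 8; at 5% it is at most 1.

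**4. Against the precision of the estimate.** These are exact binomial 95% intervals, the method the protocol names.

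- 30 subjects, 6 without measurable disease, 4 responders: 4/24 = 16.7% (4.7–37.4%) against 4/30 = 13.3% (3.8–30.7%).
- 10 subjects, 1 without measurable disease, 2 responders: 2/9 = 22.2% (2.8–60.0%) against 2/10 = 20.0% (2.5–55.6%).

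The shift is 3.4 points in the first example and 2.2 in the second. The intervals are between about 27 and 57 points wide.

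**The case against.** The case for leaving this alone has several parts.

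- **The protocol plainly assumes a target lesion.** Exclusion 2a, the imaging text and the ORR definition all do. This stands as a reading of intent, and it suggests an omission rather than a deliberate design. But an assumption does not stop anyone from enrolling.
- **The denominator is not settled.** The synopsis calculates ORR among efficacy-evaluable subjects, a term it does not define, as well as over all cases. An SAP could settle who is evaluable. This stands in part: such a subject may count, and a reader should not infer that he or she certainly will. An SAP cannot, however, undo an enrolment.
- **The size rests on assumptions.** This stands. The share is not documented, zero CR is the extreme case, and no frequency of non-measurable bone disease is given. The material gives no reason to expect the problem in the two alveolar soft part sarcoma cohorts.
- **No decision turns on it.** This stands. There is no test or threshold, and the shift is smaller than the interval width.

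A reader might also infer that DCR is diluted because stable disease is unavailable too. The documents do not support that. Section 8 describes DCR in terms of tumors that shrink or stay stable, which could take in non-CR/non-PD, whereas Section 11.3.7 counts CR, PR and SD. The protocol does not say which applies to non-target-only disease.

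**Conclusion.** The gap is real and modest. The eligibility rules, followed exactly, admit subjects who cannot reach partial response, and the analysis set and ORR denominator in Section 11 do not remove them. The loss of PR can only pull ORR down, by at most the proportion f. With the assumed 5–20% and no CR among these subjects, 20% becomes 19–16%. These are worst-case illustrations rather than forecasts, since any CR in this group shrinks the loss.

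It would be too strong to say that the trial's conclusion is at risk, that all cohorts are affected alike, or that DCR is biased. What remains is a one-directional error in the primary estimate, plausible mainly in Cohort 3, that is cheap to prevent before enrolment and cannot be prevented afterwards.

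**What to change.** Add to Section 4.1 and to the synopsis: *at least one measurable lesion per RECIST 1.1; a lesion in a previously irradiated area qualifies only if progression in it has been confirmed*. The second clause repeats the condition already in exclusion 2a, so the two sections agree.

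For any subject already enrolled without a measurable lesion, report ORR with and without that subject.

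The planned sample size does not change. The cost is that a few otherwise eligible subjects, most likely in Cohort 3, are turned away and accrual slows slightly.

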#### 4.2 Exclusion criteria for subjects

Patients with any of the following criteria will not be included in the trial:

- 1) Concomitant diseases and medical history:
- a) History or presence of other malignancy within 2 years. Patients with the following two situations can be enrolled: Other malignant tumors treated by single surgery can achieve R0 resection without recurrence and metastasis; Cured cervical carcinoma in situ, non-melanoma skin cancer, nasopharyngeal carcinoma and superficial bladder tumors [Ta (non-invasive tumor), Tis (carcinoma in situ) and T1 (tumor infiltrating basal lamina)];
- b) Unresolved toxicity greater than CTCAE Grade 1 due to any prior therapy, excluding alopecia, peripheral sensory neuropathy;
- c) Major surgical treatment or significant traumatic injury (excluding needle biopsy, endoscopic biopsy, etc.) within 28 days before the start of study treatment;
- d) Wounds or fractures that have not been healed for a long time;
- e) Hyperactive/venous thrombotic events within 6 months, such as cerebrovascular accident (including temporary ischemic attack, cerebral hemorrhage, cerebral infarction), deep venous thrombosis and pulmonary embolism;

- f) Patients with a history of psychotropic drug abuse and unable to quit or with mental disorders;
- g) Subjects with any severe and/or uncontrolled disease including:
  - 1. Unsatisfactory blood pressure control (systolic blood pressure  $\geq 150$  mmHg or diastolic blood pressure  $\geq 100$  mmHg);
  - 2. Patients with unstable angina pectoris/cardiac chest pain  $\geq$  grade 2; myocardial infarction  $\leq 12$  months before enrollment; heart failure  $\geq$  grade 1 (New York Heart Association (NYHA) classification); restrictive cardiomyopathy; atrioventricular block  $\geq$  grade 2, arrhythmia not stably controlled by drugs [including QTc  $\geq 450$  ms (male), QTc  $\geq 470$  ms (female)] and arrhythmia that may have potential impact on the trial treatment;
  - 3. Active infection ( $\geq$  CTCAE grade 2 infection);
  - 4. Decompensated cirrhosis, active hepatitis \*;  
\* Active hepatitis (hepatitis B reference: HBsAg positive, and HBV DNA  $> 2500$  copies/mL or  $> 500$  IU/mL; hepatitis C reference: HCV antibody positive, and HCV virus test value exceeds the upper limit of normal); note: eligible subjects with hepatitis B surface antigen positive or core antibody positive, hepatitis C patients, continuous antiviral therapy is recommended to prevent viral activation.
  - 5. Patients with renal failure requiring hemodialysis or peritoneal dialysis;
  - 6. History of immunodeficiency, including HIV positive or suffering from other acquired, congenital immunodeficiency diseases, or history of organ transplantation;
  - 7. Poorly controlled diabetes (fasting blood glucose (FBG)  $> 10$  mmol/L);
  - 8. Urinalysis showed urine protein  $\geq ++$ , and confirmed 24-hour urine protein  $> 1.0$  g;
  - 9. Patients with epilepsy requiring treatment;
- 2) Tumor related symptoms and treatment:
  - a) Patients who previously received surgery, chemotherapy, radiotherapy or other anti-cancer therapy 4 weeks before the start of study treatment (the washout

period will be calculated from the end time of treatment); patients who previously received local radiotherapy can be eligible if: the end of radiotherapy is more than 4 weeks from the start of study treatment (more than 2 weeks for brain radiotherapy); and the target lesion selected for this study is not in the radiotherapy area; or the target lesion is located in the radiotherapy area, but progression has been confirmed.

- b) Patients who have received Chinese patent medicines with anti-tumor indications (including compound cantharidin capsules, Kangai injection, Kanglaite capsules/injection, Aidi injection, Brucea javanica oil injection/capsules, Xiaoer Fangye/injection, cinobufotalin capsules, etc.) in the package insert of NMPA approved drugs 2 weeks before the start of study treatment;
  - c) Uncontrolled pleural effusion, pericardial effusion or ascites requiring repeated drainage (judged by the investigator);
  - d) Patients with brain metastasis whose symptom control is stable for less than 4 weeks after stopping dehydrating agents and steroid drugs;
- 3) Study Treatment Related:
- a) History of live attenuated vaccination 28 days before the start of study treatment or planned live attenuated vaccination during the study;
  - b) Previous history of severe allergy to macromolecular drugs, or allergy to known components of TQB2858 injection;
  - c) Active autoimmune disease requiring systemic therapy (eg, use of disease-modifying drugs, corticosteroids, or immunosuppressive agents) within 2 years of the start of study treatment. Replacement therapy (e.g., thyroxine, insulin, or physiological corticosteroids for adrenal or pituitary insufficiency, etc.) is not considered systemic;
  - d) Diagnosis of immunodeficiency or ongoing systemic glucocorticoid therapy or any other form of immunosuppressive therapy. (Dose > 10 mg/day prednisone or other effective hormones), and the drug is still in use 2 weeks before the first dose;

- 4) 4. Participated in other clinical trials of anti-tumor drugs;
- 5) Patients with concomitant diseases that, in the judgment of the investigator, seriously endanger the safety of the subjects or affect the completion of the study, or are considered unsuitable for the subjects for other reasons;

